### Type of data and data collection procedure

The trial will be conducted in the labour ward of maternity facilities. All women with anticipated vaginal delivery will be eligible. During the trial period information on the total number of births in the facility will be collected to monitor the recruitment efficiency. Ideally, the participating centres should enroll women 24 hours a day. However, such recruitment may not be possible at all centres.

The main data collection will be during the immediate postpartum period but women will be followed up until discharge from the hospital to record any additional interventions and complications that may occur. Once the bleeding stops and the woman is ready for transfer to the postnatal ward the researcher will fill the data collection form. After discharge the data collection forms will be completed and the form data will be entered on to the online system. The online data entry will be either at the hospital or country level depending on local capacity.

### Analysis plan

The main analysis will be on an intention-to-treat principle with comparisons made between the 'simplified' and 'full' AMTSL packages for primary and secondary outcomes. An alternative to the ITT analysis (non-ITT analysis, sometimes called 'per-protocol'), that excludes patients not on their intended treatment and/or those who are not protocol-compliant in any other way could bias the trial in either direction, depending on which patients are thus excluded. In non-inferiority and equivalence trials, performing non-ITT analysis in addition to ITT analysis is desirable as a protection from the increase in type I error risk.

We expect only a small number of protocol deviations because the personnel involved in the study will receive intensive and continuous training and because the trial will be closely monitored by trial investigators and periodically by a Data Monitoring Committee that will look at protocol deviations. Thus, the decrease in power due to exclusions of protocol deviations will be minimal. Table 1 shows that for the proposed sample size, the power is higher than the usually required 80%.

There may be deviations from the trial protocol if the baby's condition requires urgent action. In such situations the cord may be clamped and cut immediately after birth of the head and if the caregiver is involved in the resuscitation the timing of placental delivery may differ (this could be in either direction). We would expect this deviation to be equally distributed in the two groups. A second type of deviation could occur if a woman who has earlier given consent and randomly allocated to one group withdraws her consent after randomization. The withdrawal of consent after random allocation should be extremely rare since the random allocation will be made when vaginal delivery is imminent We have looked at earlier trials where expectant management was used (because expectant management omits controlled cord traction) and did not find any suggestion that there was a compliance problem with omission of CCT. Nevertheless, the sample size calculation has a margin of additional power as mentioned in table 2 to ensure that such protocol deviations do not have a negative impact on the conclusions[17]

**Table 2 T2:** CONSORT recommendations in the protocol – Checklist for non-inferiority and equivalence trials. Items 1 through 12[17]

Paper section and topic	Item	Descriptor	Reported on section
TITLE & ABSTRACT	1	How participants were allocated to interventions (*e.g*., "random allocation", "randomized", or "randomly assigned"), *specifying that the trial is a non-inferiority or equivalence trial*.	Title in cover page. Summary: section 1

*INTRODUCTION *Background	2	Scientific background and explanation of rationale, *including the rationale for using a non-inferiority or equivalence design*.	2 and 3. In particular, see 2.1.5, two last paragraphs for rationale for non-inferiority

*METHODS *Participants	3	Eligibility criteria for participants *(detailing whether participants in the non-inferiority or equivalence trial are similar to those in any trial(s) that established efficacy of the reference treatment) *and the settings and locations where the data were collected.	4.3 and 4.4.3

Interventions	4	Precise details of the interventions intended for each group *detailing whether the reference treatment in the non-inferiority or equivalence trial is identical (or very similar) to that in any trial(s) that established efficacy*, and how and when they were actually administered.	4.1

Objectives	5	Specific objectives and hypotheses, *including the hypothesis concerning non-inferiority or equivalence*.	3

Outcomes	6	Clearly defined primary and secondary outcome measures *detailing whether the outcomes in the non-inferiority or equivalence trial are identical (or very similar) to those in any trial(s) that established efficacy of the reference treatment *and, when applicable, any methods used to enhance the quality of measurements (*e.g*., multiple observations, training of assessors).	4.2

Sample size	7	How sample size was determined *detailing whether it was calculated using a non-inferiority or equivalence criterion and specifying the margin of equivalence with the rationale for its choice*. When applicable, explanation of any interim analyses and stopping rules (*and whether related to a non-inferiority or equivalence hypothesis*).	4.4.3

Randomization – Sequence generation	8	Method used to generate the random allocation sequence, including details of any restrictions (*e.g*., blocking, stratification)	4.4.1

Randomization – Allocation concealment	9	Method used to implement the random allocation sequence (*e.g*., numbered containers or central telephone), clarifying whether the sequence was concealed until interventions were assigned.	4.4.2

Randomization – Implementation	10	Who generated the allocation sequence, who enrolled participants, and who assigned participants to their groups.	4.4.2

Blinding (masking)	11	Whether or not participants, those administering the interventions, and those assessing the outcomes were blinded to group assignment. If done, how the success of blinding was evaluated.	4 (last sentence before 3.1)

Statistical methods	12	Statistical methods used to compare groups for primary outcome(s), *specifying whether a one or two-sided confidence interval approach was used*. Methods for additional analyses, such as subgroup analyses and adjusted analyses.	4.4.3 & 4.5

The actual management of third stage of labour will be recorded in all women to enable the analysis mentioned above.

Comparisons will be expressed as relative risks and risk differences with 95% confidence intervals. The analysis will be stratified by site, and if there is heterogeneity between the sites for any of the results possible causes of heterogeneity will be explored. In the presence of heterogeneity, the results will not be combined in a single summary estimate (or pooled estimate). In the absence of heterogeneity at the 5% level, the results will be combined.

The primary analysis will follow the following scheme for interpretation (Figure 1):[18] If the lower limit of the 95% confidence interval lies to the right of the non-inferiority margin (Δ) the experimental intervention will be declared "inferior" (situation H). Situations A-D indicate non-inferiority with respect to the pre-stated margin Δ. Situations E-G are inconclusive, although E and F are not likely to occur because the trial size guarantees sufficient power. If the results are inconclusive regarding the non-inferiority hypothesis and the whole 95% confidence interval lies to the right of zero (situation G), it will be concluded that the limited package was statistically significantly worse according to a superiority hypothesis.

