### Objective

The primary objective is to determine whether the simplified package of oxytocin 10 IU IM/IV, without CCT, is not less effective than the full AMTSL package with regard to reducing blood loss ≥ 1000 ml in the third stage of labour. The hypothesis will be that of non-inferiority within a margin of 0.45 to 0.50%. If this hypothesis is demonstrated, the simplified package without CCT could be adopted, with the advantage of not requiring training to acquire the manual skill to perform this task.

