The expectant management sPPH rate was more difficult to estimate because the data was only available from earlier published trials and blood loss estimation methods and the actual expectant management method differed between trials. Values between 3.0 to 4.0% are considered realistic and used for sample size estimations.

Table 1 includes different scenarios for the calculation of sample size, obtained by varying the sPPH rate with expectant management (3.0 to 4.0%) and varying the % retained effect (70% to 80%), assuming a fixed 1.5% sPPH rate for the full AMTSL package. These different scenarios result in different choices of the margin of non-inferiority **Δ**. The total sample size required for a non-inferiority test at the 2.5% level using a two-sided 95% confidence interval and a power of 80% is shown, as well as the power obtained for fixed sample sizes of 20,000 and 25,000.

**Table 1 T1:** Sample size scenarios

Blood loss ≥ 1000 ml with full amtsl	Blood loss ≥ 1000 ml with Expectant	Estimated impact of Full AMTSL	Proportion (of full AMTSL effect) retained by the simplified package	Δ (Difference to exclude to claim equivalence)	Total N for 80% Power	Power with total N = 20,000	Power with total N = 25,000
1.5	3.0	1.5	0.7	0.45	22,908	75%	83%

1.5	3.5	2.0	0.75	0.50	18,555	83%	90%

1.5	4.0	2.5	0.8	0.50	18,555	83%	90%

A trial of 22,908 women will have 80% power to show non-inferiority of the simplified package within 0.45% of the full AMTSL package sPPH rate (i.e. less than 1.95% sPPH rate), with a level of significance of 2.5% (Table 1, row 1). The estimates from the centres that have expressed interest in participating in the trial indicate that approximately 20,000–25,000 women can be recruited in a 12 months recruitment period. These centres have collaborated with WHO before and have experience in third stage trials.

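### Spare power is offered as protection against protocol deviations, but it cannot protect the ITT non-inferiority claim from cross-over, and the decision scheme is stated only for the primary (ITT) analysis

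*Protocol article*

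**What the plan says.** All of this is in the protocol article, mostly under Analysis plan.

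- The main analysis is by intention to treat. A non-ITT analysis is described in general terms as one "that excludes patients not on their intended treatment and/or those who are not protocol-compliant in any other way", with the warning that such exclusions can bias the result in either direction.
- On the need for it: "performing non-ITT analysis in addition to ITT analysis is desirable as a protection from the increase in type I error risk".
- Few deviations are expected, and the loss of power from excluding them is called minimal, with Table 1 cited in support.
- Three sources of deviation are discussed: urgent newborn care, withdrawal of consent after allocation, and compliance with omitting cord traction. The last is said to have caused no apparent problem in earlier trials of expectant management.
- The paragraph closes by saying that "the sample size calculation has a margin of additional power as mentioned in table 2 to ensure that such protocol deviations do not" damage the conclusions. Table 2 is the CONSORT checklist.
- Actual third-stage management will be recorded for every woman so that the non-ITT analysis can be done.
- The rule for the verdict is introduced with "The primary analysis will follow the following scheme for interpretation", followed by situations A to H. The text does not say whether the non-ITT result must also meet the margin.

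**The concern.** Power guards against failing to show non-inferiority when it is true. The error that deviations threaten in a non-inferiority trial is the opposite one: claiming non-inferiority when it is false. The two packages differ only in how the placenta is delivered. Traction in the simplified arm, or its omission in the full arm, therefore makes the arms more alike and pulls the ITT difference toward zero. An equal share of deviations in each arm does not prevent this. A larger sample narrows the interval around a diluted difference; it does not undo the dilution.

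The plan recognises the type I error risk and names the non-ITT analysis as the protection. But the A–H scheme is attached to the primary analysis, which is ITT. At stake is whether the 2.5% error rate behind a recommendation to drop cord traction is the one the trial actually has.

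**Working it through.** **Inputs.** From the sample size section: "a non-inferiority test at the 2.5% level using a two-sided 95% confidence interval and a power of 80% is shown"; "assuming a fixed 1.5% sPPH rate for the full AMTSL package"; total N of 20,000 to 25,000. From Objective: "The hypothesis will be that of non-inferiority within a margin of 0.45 to 0.50" percent. Allocation is taken as 1:1; the ratio is not stated, but 1:1 reproduces the table. The cross-over rate c is **an assumption**, since the document gives none. It is the net share, summed over both arms, of women managed as in the other arm.

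**Step 1: reproduce Table 1.** Total N = 2 × 2p(1−p)(1.96 + 0.8416)²/Δ² with p = 0.015.
- Δ = 0.45 points: 22,908 (stated: 22,908).
- Δ = 0.50 points: 18,556 (stated: 18,555, a rounding difference).

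Power = Φ(Δ/SE − 1.96), with SE = √(2p(1−p)/(N/2)).
- N = 25,000: SE = 0.1538 points; power 83.3% (Δ 0.45) and 90.2% (Δ 0.50).
- N = 20,000: SE = 0.1719 points; power 74.5% and 82.9%.

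These match the stated 83%, 90%, 75% and 83%.

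**Step 2: false non-inferiority rate under cross-over.** Let the true difference under full adherence equal Δ. The ITT difference is then Δ(1−c), and the false claim rate is Φ(cΔ/SE − 1.96). Here SE uses 1.5% in the full arm and 1.5% + Δ(1−c) in the simplified arm. For Δ = 0.45 points:

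| c (assumed) | ITT difference (points) | SE at 25,000 (points) | False claim, N = 25,000 | False claim, N = 20,000 |
|---|---|---|---|---|
| 0 | 0.450 | – | 2.5% | 2.5% |
| 2% | 0.441 | 0.1645 | Φ(−1.905) = 2.8% | 2.8% |
| 5% | 0.4275 | 0.1641 | Φ(−1.823) = 3.4% | 3.3% |
| 10% | 0.405 | 0.1636 | Φ(−1.685) = 4.6% | 4.3% |
| 20% | 0.360 | 0.1626 | Φ(−1.406) = 8.0% | 7.1% |

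Splitting the cross-over between arms changes little (7.9% instead of 8.0% in the last row at 25,000). A simulation of 1,000,000 trials per setting, with the split version at 25,000, gave 2.6%, 4.7% and 8.0% at c = 0, 10% and 20%. With Δ = 0.50 and cross-over split between arms, the rates at 25,000 are 3.5%, 4.9% and 8.7% for c = 5%, 10% and 20%.

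**Step 3: what spare power can do.** If the packages are truly equal, cross-over leaves the ITT difference at zero and costs the ITT analysis no power, so spare power has nothing to repair there. It can replace women excluded from a non-ITT analysis. The share that can be excluded before power drops below 80% is:
- N = 25,000: 1 − 22,908/25,000 = 8.4% (Δ 0.45); 1 − 18,555/25,000 = 25.8% (Δ 0.50).
- N = 20,000: none (Δ 0.45, already 75%); 1 − 18,555/20,000 = 7.2% (Δ 0.50).

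**Step 4: per-protocol power at Δ 0.45**, from the Step 1 formula with N reduced by the exclusions:

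| Exclusions | N = 25,000 | N = 20,000 |
|---|---|---|
| 0 | 83% | 75% (74.5%) |
| 5% | 81% | 72% |
| 10% | 79% | 70% |

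**The case against.** **Spare power was meant for exclusions.** The preceding paragraph speaks of power lost to exclusions and cites Table 1, so the later sentence may simply repeat that. Step 3 shows this use is sound at 25,000. But the sentence directly before it is about compliance with omitting cord traction, and the claim is made for the conclusions in general. As worded it covers cross-over, and there it is wrong.

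**The plan expects few deviations.** This stands. At 1–2% net cross-over the error rate is only about 2.7–2.8%. A reader might infer that the nominal rate survives only with near-perfect adherence; the figures do not support that.

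**The non-ITT analysis may be given its role elsewhere.** This article condenses a fuller protocol, and an analysis plan may exist. A reader might infer that the non-ITT analysis will be ignored; nothing says so, and the data for it are collected. The narrower point is that the published verdict rule refers to the primary analysis alone, although the same section names the non-ITT analysis as the protection.

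**Two further readings go too far.** One is that the described exclusions would remove bleeding women from the simplified arm. The phrase is a generic description of non-ITT analysis, not this trial's definition, and the plan itself warns of bias in either direction. The other is that a larger trial makes matters much worse. The direction is right, but between 20,000 and 25,000 the increase is only 0.1–0.3 points at 5–10% cross-over.

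**Conclusion.** The point holds in a limited form. The sentence offering additional power as protection against deviations is wrong for cross-over and cites the wrong table. The protection the plan does name is absent from the verdict rule stated in this document. With a true excess equal to Δ = 0.45 points and 25,000 women, the false non-inferiority rate goes from 2.5% to about 2.8%, 3.4%, 4.6% and 8.0% at 2%, 5%, 10% and 20% net cross-over. These rates are assumptions. The calculation also supposes that women who cross over have the risk of the package they actually received. Deviations that do not make placental delivery more alike in the two arms do not inflate the error this way. The inflation is negligible to small at the deviation rates the plan hopes for and matters from about 5–10%.

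**What to change.** 1. Reword the sentence on additional power so that it covers only women excluded from the non-ITT analysis, and cite Table 1.
2. State that non-inferiority is declared only if the upper limit of the 95% confidence interval lies below Δ in both the ITT and the non-ITT analysis.
3. Define the non-ITT set in advance by the placental delivery method first attempted, so that exclusion does not depend on bleeding that follows. This defines an analysis set and changes nothing in care.

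The change is one of wording, and actual management is already recorded for all women. The real cost is power for the joint claim, which cannot exceed the per-protocol power in Step 4. At Δ 0.45 and 25,000 women the loss is modest. At 20,000, the low end of the recruitment range, power is below 80% before any exclusion and falls further with them, so the recruitment target matters more under the joint rule. A non-ITT comparison is also not fully protected by randomization; it therefore supplements the ITT result and does not replace it.

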**Methods:**

A hospital-based, multicentre, individually randomized controlled trial is proposed. The hypothesis tested will be a non-inferiority hypothesis. The aim will be to determine whether the simplified package without CCT, with the advantage of not requiring training to acquire the manual skill to perform this task, is not less effective than the full AMTSL package with regard to reducing blood loss in the third stage of labour.

The simplified package will include uterotonic (oxytocin 10 IU IM) injection after delivery of the baby and cord clamping and cutting at approximately 3 minutes after birth. The full package will include the uterotonic injection (oxytocin 10 IU IM), controlled cord traction following observation of uterine contraction and cord clamping and cutting at approximately 3 minutes after birth. The primary outcome measure is blood loss of 1000 ml or more at one hour and up to two hours for women who continue to bleed after one hour. The secondary outcomes are blood transfusion, the use of additional uterotonics and measure of severe morbidity and maternal death.

We aim to recruit 25,000 women delivering vaginally in health facilities in eight countries within a 12 month recruitment period.

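### The pooled primary result is withheld when a 5% test for site heterogeneity is significant, and the plan gives no rule for the primary conclusion in that case

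*Protocol article*

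**What the plan says.** The Analysis plan section of the protocol article stratifies the analysis by site and sets two branches. When sites differ: "In the presence of heterogeneity, the results will not be combined in a single summary estimate (or pooled estimate"). Otherwise: "In the absence of heterogeneity at the 5% level, the results will be combined". The rule is worded to cover all results, so the primary outcome is included. The only action named for a significant test is to look for causes.

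The next paragraph says how the primary analysis will be read. Situations A to H of Figure 1 each place one 95% confidence interval against the margin and zero. None covers a result that has not been pooled.

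On power, the sample size section describes a "non-inferiority test at the 2.5% level using a two-sided 95% confidence interval and a power of 80" per cent, "assuming a fixed 1.5% sPPH rate for the full AMTSL package". It then states: "A trial of 22,908 women will have 80% power to show non-inferiority of the simplified package within 0.45" per cent. The Analysis plan adds: "Table 1 shows that for the proposed sample size, the power is higher than the usually required 80" per cent, and relies on that spare power to absorb protocol deviations. The Objective section gives a range for the margin: "The hypothesis will be that of non-inferiority within a margin of 0.45 to 0.50" per cent. The recruitment target in the abstract is 25,000 women in eight countries.

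**The concern.** The primary test takes place only if a preliminary test is non-significant. The power in Table 1 is that of a pooled test that is always done. If the preliminary test is significant, by chance or because sites really differ, the interval that Figure 1 needs does not exist and the plan states nothing in its place. A trial of 25,000 women could then finish without a primary conclusion.

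Site differences are also foreseeable here. Under both packages, each centre decides in advance whether to use uterine massage. The Stratified analysis section plans to examine whether massage interacts with cord traction, and the rationale for the intervention says that interactions between components cannot be ruled out. The plan therefore builds in a possible source of between-centre variation and would give up its pooled estimate if that variation were detected.

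**Working it through.** **Inputs from the protocol article.** Severe haemorrhage rate 1.5% with the full package; one-sided 2.5% level read from a two-sided 95% interval; margin Δ of 0.45 or 0.50 percentage points; N of 22,908 or 25,000; eight centres; heterogeneity test at 5%.

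**Assumptions.** Same 1.5% rate in both arms and 1:1 allocation (together these reproduce Table 1); eight equal centres; Cochran's Q on 7 degrees of freedom, because the article names no test; no dropout.

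**1. Reproduce Table 1.** Total N = 4 × 0.015 × 0.985 × ((1.960 + 0.8416)/Δ)².
- Δ = 0.0045: 22,907.1, which is 22,908 with whole women per arm (stated 22,908).
- Δ = 0.0050: 18,554.7 (stated 18,555).

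Power = Φ(Δ/SE − 1.96), with SE = √(2 × 0.015 × 0.985/(N/2)).
- N 22,908, Δ 0.45: SE 0.1606 points; Φ(2.802 − 1.960) = 80.0%.
- N 25,000, Δ 0.45: SE 0.1538 points; Φ(2.927 − 1.960) = 83.3% (stated 83%).
- N 25,000, Δ 0.50: Φ(3.252 − 1.960) = 90.2% (stated 90%).

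The sample size arithmetic is sound.

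**2. Apply the rule with the same effect at every site.** If the preliminary test has exact 5% size and is independent of the pooled estimate, power is multiplied by 0.95. The simulation column shows the chance that the pooled upper limit is below Δ and Q is non-significant. It used 40,000 trials per scenario, with Q on the log relative risk or the risk difference, and control rates equal or varying between centres.

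| N, Δ | Table 1 power | × 0.95 | Simulated |
|---|---|---|---|
| 22,908, 0.45 | 80.0% | 76.0% | about 77% |
| 25,000, 0.45 | 83.3% | 79.2% | 79–81% |
| 25,000, 0.50 | 90.2% | 85.7% | 86–87% |

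The simulated values are slightly higher because Q rejects in only about 3 to 5% of trials at these event counts.

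**3. Can one site stand in?** 25,000/8 = 3,125 women, or 1,562.5 per arm, with about 25,000 × 0.015/8 = 47 events. SE = √(2 × 0.015 × 0.985/1,562.5) = 0.435 points, so the 95% interval is ±0.85 points. Power is Φ(0.45/0.435 − 1.96) = 17.7%, or Φ(0.50/0.435 − 1.96) = 20.9%.

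**4. Apply the rule when sites truly differ.** The documents give no between-site variance. The SD of the log relative risk is therefore assumed, with the site effects scaled so that the average risk difference is zero. At SD 0.2 the pooled result is lost in about 15 to 20% of trials.

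| N, Δ | SD 0.1 | SD 0.2 | SD 0.3 |
|---|---|---|---|
| 22,908, 0.45 | 75–76% | 66–68% | 50–53% |
| 25,000, 0.45 | 78–79% | 67–70% | 50–53% |
| 25,000, 0.50 | 84–85% | 73–75% | 53–57% |

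With this scaling, power without the rule stays at about 80%, 83% and 90%, so the whole loss comes from the rule.

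**5. False claims.** With the true difference set at 0.45 points at every site and N = 25,000, non-inferiority was declared in about 2.6% of simulated trials when pooling was unconditional, and in about 2.5% under the rule.

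**The case against.** Refusing to average materially different effects is a reasoned choice, especially when centres differ in their use of massage. The rule can only remove a claim of non-inferiority and never adds one. With a common effect the cost is at most about one trial in twenty left inconclusive. The wording bars a single summary estimate, which does not plainly forbid summaries within massage strata. Centre sizes are not given, and a large centre could be more informative than step 3 suggests.

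Most of this stands as a limit on the point. None of it supplies the missing primary conclusion: summaries by massage use are not named as a fallback, and the plan itself expects that analysis to be underpowered.

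Stronger readings are tempting but not supported:
- **Power falls below 80% throughout.** At 25,000 it sits at the 80% line for Δ 0.45 and remains about 86% for Δ 0.50 with a common effect.
- **The rule inflates the type I error.** Step 5 shows that it does not.
- **The unnamed scale of the heterogeneity test is itself a fault.** Scale is commonly left to a statistical analysis plan, which is not shown.
- **No single site could ever conclude anything.** The figure is about 18 to 21% power under equal sizes, which is low but not zero.

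**Conclusion.** The point holds in a limited form. The protocol positively states a rule that can take away its own primary result, and it provides no conclusion for that case, although Figure 1 needs one interval.

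With a common effect, up to about 5% of trials are affected. The power loss is about 3 to 5 percentage points, and power is clearly below 80% only at N 22,908 with Δ 0.45. At N 25,000 with Δ 0.45 the spare power over 80% is 3.3 points (83.3 − 80), and the rule uses roughly all of it (83.3 − 79.2 = 4.1 points by the exact 5% calculation). That spare power is what the plan sets aside for protocol deviations.

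With real variation the loss is large: at an assumed SD of 0.2, power is about 66 to 75% across the three scenarios. These figures rest on eight equal centres, Cochran's Q and an average effect of zero. If the site effects did not average to zero, some power would be lost even with unconditional pooling, and changing the rule would not recover that part.

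The consequence is an unanswered primary question, not a wrong answer.

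**What to change.** Replace the two conditional sentences. State that the primary result is always the site-stratified risk difference over all sites (for example Mantel-Haenszel), with its 95% confidence interval judged against the margin. Report the site estimates and a treatment-by-site test as supportive. A significant test then prompts exploration of causes, including massage use, and does not withdraw the pooled result.

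This restores the power in Table 1 under its own assumptions. It costs two sentences in the protocol and the matching text in any analysis plan, needs no extra data, and should be settled before results by arm are seen. There is one small drawback: if effects really differ, the pooled figure is an average over sites and must be shown beside the site estimates.
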